#### Experimental intervention (SOAR program)

SOAR is a 6-month, digital (remote videoconferencing delivery*)*, physiotherapist-guided knee health program that promotes exercise behavior and self-management ability. SOAR was designed iteratively with a complex intervention framework [79] and reflects consensus recommendations [38] and principles that promote positive healthcare experiences and meaningful outcomes (person-centered care [44], shared decision-making [80], behavior change theory [81]). The rationale for physiotherapist delivery is patient preference and scope for safe and effective knee injury exercise prescription [40, 74]. The rationale for virtual delivery is access [82], scheduling flexibility [83], enhanced patient-physiotherapist relationship through continuity and consistency of care [55, 84], and cost-effectiveness [85]. Virtual physiotherapist exam and treatment do not differ from in-person methods for pain, function, and quality-of-life outcomes [86, 87]. Prior to beginning the SOAR program, participants are provided with a workbook containing an overview of the study and SOAR program, educational materials, instructions for rating perceived effort, SMART (specific, measurable, attainable, relevant, time-bound) goal setting, Fitbit use, and exercise log.

SOAR has three components: one-time Knee Camp, tailored weekly home-based program with tracking, and weekly 1:1 physiotherapist-guided counseling. Participants will be randomly allocated to 1 of 4 independent musculoskeletal physiotherapists (licenced, certified in Brief Action Planning [88], and trained and delivered SOAR in our pilot RCT [54]).

Knee camp: This 2-h session involves interactive group education, 1:1 knee exam, and 1:1 exercise therapy and activity counseling. Education topics are patient partner approved, consistent with shared decision-making [89], practice guidelines [90], and programs promoting self-management [91]. During the knee exam, participants and physiotherapists will co-identify and prioritize individual residual functional deficits. Exercise therapy and activity counseling will follow a motivational interviewing Brief Action Planning approach [88]. Physiotherapists will guide participants to identify at least one home-based exercise therapy and one physical activity SMART goal with tasks and adequate dose (target Rating of Perceived Effort) [92, 93] tailored to their unique needs. Goals are modified until participant’s confidence to execute them rates $$\ge$$ 7/10. Actions to address perceived barriers are discussed.

Weekly home-based program with tracking: Participants will work towards their exercise therapy and activity goals at home. To self-monitor (track) exercise therapy and activity, participants will log exercise completion, Rating of Perceived Effort, and pain (paper or electronic form), and use a commercial wrist activity monitor (Fitbit®, worn 24 h/day) that wirelessly synchronizes to an online dashboard. Exercise logs are a valued active coping strategy after injury [25], and activity trackers provide motivation for activity goals [94, 95]. These data will be used for self-monitoring purposes, to inform weekly physiotherapist-guided counseling sessions, and monitor participant adherence.

Weekly physiotherapist-guided exercise therapy and physical activity counseling sessions: Aligned with patient preferences for regular contact with a licensed clinician with exercise prescription expertise for health conditions [25, 26, 96], participants will attend a 1:1 virtual physiotherapy counseling session (weekly months 0–4, bi-weekly months 5–6)*.* During counseling sessions (~ 15 min), participants and physiotherapists will progressively add and modify personalized SMART exercise therapy and activity goals, considering goal completion, exercise and activity tracking data from the past week, successes, and obstacles encountered [94].

Rationale for SOAR elements: Capability, opportunity, and motivation interact to generate exercise behaviors (COM-B model) [81, 97]. Exercise interventions that incorporate tailoring and the behavioral change techniques of goal setting, intentional and reflective self-monitoring, and performance feedback produced larger effects than those that do not [98, 99]. In the context of SOAR, exercise therapy and activity are the active ingredients for modifying knee health, while other program elements support their execution by promoting psychological capability (education), physical (virtual delivery) and social (alliance with physiotherapist and between participants) opportunity, and automatic (tailored exercise/activity) or reflexive (goal setting, action planning, self-monitoring) motivation [24, 88, 97, 100–103].

#### Comparison intervention

Knowing that the choice of control condition will affect intervention effect size [104], we developed a control minimal intervention with the CoPPS Checklist for Control Intervention and Conduct [67]. The control intervention aims to provide an expectation of therapeutic benefit, while controlling for natural history, regression to the mean, and contextual effects [105], while acknowledging that more elaborate control conditions can mask effectiveness [106].

Control group participants will receive resources to facilitate an unsupervised home exercise program inert of tailoring, goal setting, intentional and reflective self-monitoring, or performance feedback. This includes the same activity tracker and resistance loop set; unlimited access to a 30-min educational video and best-practice workbook (broad exercise principles for ACLR); and 1 virtual session with a control physiotherapist (naïve to SOAR and Brief Action Planning) trained to explain and answer questions about materials but not volunteer further information.

The control intervention replicates many SOAR elements, including materials, provider, delivery method, location, and some (online learning, tracking, physiotherapist interaction), but not all attention (frequency) to ensure it is inert of behavioral change techniques that increase exercise effect. A minimal attention control was chosen over usual care (0.5 knee health visits annually after discharge from ACLR rehabilitation) [23] to reduce overestimating treatment effect; with that said, minimal attention control conditions are common in rehabilitation trials [107–109], enable long-term follow-up, and facilitate data synthesis [107, 110].

### Data collection procedures {11d, 18a, b}

Participants will be evaluated at baseline and 6- (primary endpoint), 12-, and 24-months (see Table 2). At all timepoints, participants will complete patient-reported outcomes using the online REDCap [77] platform and attend an in-person testing session at UBC. At the in-person session, participants will complete a computerized dynamometry assessment of knee muscle function, a bioelectrical impedance scan, and be given a triaxial accelerometer (ActiGraph wGT3X-BT®, Actigraph™, Pensacola, FL, USA) and instructed to wear it for 7 full days before returning it in a pre-paid courier envelope. The option to complete patient-reported outcomes on paper at the in-person sessions will also be offered.

At baseline, 12-, and 24-month follow-up sessions, participants will also attend a 1-hour visit to the MRI Research Centre at UBC, where dedicated technicians will collect MRI studies of the ACLR knee. Healthcare resource use (including co-interventions), monthly step count, and adverse, seriously adverse, and unexpected events will be assessed monthly over the entire study period using a 7-question short message service (SMS) screening survey and follow-up phone calls as appropriate (see below).

### Outcomes {12}

Outcome choice is based on previous research and responsiveness observed during our feasibility and pilot studies [18, 29, 53–55, 111]. Patient and clinician partner guidance about the relevance, meaningfulness, and burden of measures has also been sought. Table 2 provides an overview of the outcomes and timeline of collection.

Baseline characteristics: age, sex, gender, ethnicity, education level, employment status, socioeconomic status (SES; annual household income, postal code), pre-ACL tear activity level, sports participation, and previous knee injury (treatment), ACL tear (concomitant injury/surgery/rehabilitation), and medical history details will be collected [52]. Baseline body mass index (BMI) will be calculated from height (stadiometer) and body mass (Model MC-980U +, Tanita Inc, USA).

#### Primary outcome

##### Aggregate of knee-related pain, symptoms, function in sport and recreation and QOL

The primary outcome is between-group difference in the change in an aggregate measure of knee-related pain, symptoms, function in sport, and QOL from baseline to 6-month follow-up. The KOOS is a valid and reliable patient-reported outcome with sub-scales for pain, other symptoms, daily living function (ADL), sport/recreation function, and QOL across knee injury and OA populations [112]. The KOOS_4_ (average of 4 sub-scales omitting ADL) is a recommended and accepted primary outcome for ACLR RCTs [38, 57, 58, 107] and was responsive in our pilot RCT [54].

#### Secondary outcomes

##### Knee-related pain, symptoms, function in sport and recreation and QOL

To help interpret the clinical relevance of the KOOS_4_, individual sub-scale scores and the percentage of participants exceeding sub-scale PASS [113] scores (pain 89; symptoms 83; ADL 95, sport 72; QoL 73) [38] will be reported by group and timepoint.

#### Perceived self-management

The 12-item Partner in Health Scale (PIH) is a valid and reliable patient-reported outcome measure of self-management across numerous chronic conditions [114, 115] with subscales for knowledge, symptom recognition and management, partner in treatment, and coping [115]. Each subscale item is scored on a 9-point scale, and individual subscale items are summed, with lower scores indicating a better ability to self-manage. The change in PIH between timepoints will be reported.

#### MRI features of osteoarthritis

Knee OA features (e.g., cartilage defects, bone marrow lesions, meniscal tears, osteophytes) on axial, sagittal, and coronal 3D proton-density gradient MRI sequences (3 T scanner, Philips Elition, 8-channel knee coil) will be registered using the valid semi-quantitative MRI OA knee score (MOAKS) [59, 116]. Positioning aids will immobilize the knee to ensure consistent scans [18, 111]. A radiology fellow (supervised by AS) will conduct MOAKS ratings blinded to group allocation. OA feature worsening will be defined as an increase in the size of the lesion using established methods [116]. Changes in MRI features between baseline, 12, and 24 months will be reported.

#### Participant and provider perceived barriers and facilitators of SOAR delivery

On completion of the SOAR program, we will conduct semi-structured 1:1 recorded interviews with all physiotherapists and a purposive maximum variation [117] sample of 15–20 SOAR participants (varied by gender, age, time from ACLR, adherence). Using an inductive approach and interview guide, open-ended queries about SOAR barriers and facilitators will be asked. We will explore therapeutic alliance, goal completion, and self-management with participants, and Brief Action Planning training, and perceived impacts on patient and clinic flow with physiotherapists. We will pilot, then refine interview guides co-developed with patient and physiotherapist partners during data collection to support thorough exploration of emerging themes. Probes/prompts will promote elaboration. Field notes will be taken. Sampling will be informed by ongoing analyses and cease when no new themes arise [117, 118]. Participants will also respond to an online survey where they can anonymously share their satisfaction with the SOAR program.

#### Incremental cost-utility ratio

To assess the value for money (healthcare system perspective) of the SOAR program, we will estimate the incremental cost per quality-adjusted life years (QALY) gained by SOAR versus the control intervention at intervention cessation and end of follow-up. Costs will be estimated with a HRU questionnaire [119], as the study population often uses resources not captured in administrative data [23], and evidence of good agreement between administrative and prospectively collected HRU data [120, 121]. The HRU captures provider visits, hospital admissions, lab and diagnostic tests, and medication use. The HRU will be administered by research staff monthly via a 7-question SMS with phone call follow-up as needed over the study period.

QALYs will be estimated from health-related QOL (EQ-5D-5L) [122, 123] using area under the curve analysis. The EQ-5D-5L (European Quality of Life 5 Dimensions 5 Level) is widely used for cost-utility analyses across multiple countries and conditions [124, 125] (including OA [126, 127]), and assesses five levels across five health domains (anxiety/depression, pain/discomfort, mobility, self-care, usual activities) to produce a health state profile using Canadian conversion tariffs [128].

### Exploratory outcomes

Exploratory outcomes will be reported at all timepoints unless otherwise indicated.

#### Self-reported function

The Patient Specific Functional Scale (PSFS) will be used to assess changes in functional limitations most relevant to participants [129]. The PSFS prompts participants to identify three activities important to them and rate their ability to perform each activity on a 10-point numerical rating scale. Individual scale scores are summed and transformed to a 0–100 scale with higher scores indicating better outcomes. The PSFS is valid and reliable for use in persons with knee injury [129].

#### Knee-specific self-efficacy

The Knee-Specific Self-Efficacy Scale (KSES)[130] is a valid and reliable measure of knee-specific self-efficacy in people with a sport-related knee injury in the previous 5 years [131]. The KSES consists of 22 items organized into two sub-scales (present and future self-efficacy) [130]. Each item is scored on a 0–10-point Likert scale, with higher scores indicating great confidence. Individual item scores are summed to produce a total score. Higher scores indicate higher levels of self-efficacy [130].

#### Fear of movement and re-injury

The Tampa Scale of Kinesiophobia (TSK) is an 11-item questionnaire that measures fear of movement and reinjury [132]. Each item is scored on a Likert scale from strongly disagree to strongly agree. The item scores are summed to produce a total score, with a higher value indicating greater fear. The TSK has evidence of known-groups validity (scores discriminate between athletes who return or did not return to sports participation level after knee injury) [133].

#### ACL-related quality of life

The ACL Quality-of-Life Questionnaire (ACLQOL) is a 32-item questionnaire that measures knee-related quality of life in individuals who have had an ACL tear [134]. The ACLQOL consists of 5 domains related to physical symptoms (5 items), occupation (4 items), recreational activities (12 items), lifestyle (6 items), and social interactions (5 items). Each item is rated on a scale from 0 to 100, and the total score is expressed as an average across domains out of 100%, with higher scores indicating greater knee-related quality of life. The ACLQOL is valid, responsive to change, and has excellent test–retest reliability [134].

#### Self-reported physical activity

The Godin Leisure-Time Exercise Questionnaire (GLTQ) is a 3-item questionnaire that provides a valid and reliable assessment of metabolic equivalents of physical activity during free (or leisure) time [135, 136]. There are established thresholds for sufficient and insufficient leisure time activity based on GLTQ outcomes [135].

#### Daily average moderate to vigorous physical activity

Total daily minutes of moderate to vigorous physical activity will be estimated from a waist-worn tri-axial accelerometer (ActiGraph GT3X®, Actigraph, Pensacola, FL, USA) worn for 7 consecutive days [137]. Participants will wear the device 24 h a day, removing it only for bathing/swimming activities and keep a log of the duration and intensity of non-wear time activities. The average number of 10-min moderate-to-vigorous physical activity bouts [33] over 7 days is a valid and reliable measure of activity in youth and young adult populations [51].

#### Knee extension and flexion strength

Isokinetic peak concentric knee extensor and flexor torque (Nm/kg) will be assessed with a computerized dynamometer (Biodex System 4™, Shirley, NY, USA) at 90°/s over 0–100° of knee motion. The peak gravity-corrected torque reached across 3 repetitions will be recorded and normalized to body weight. These outcomes are reliable, valid, relevant, and recommended measures of muscle function [138].

#### Adiposity

Bioelectrical Impedance (Model MC-980U +, Tanita Inc., USA) is a feasible method for assessing and tracking body composition in clinical settings and will be used to measure total body mass and total fat mass. Bioelectrical impedance has been shown to be valid and reliable in child, youth, and adult populations [139, 140]. The device will be calibrated prior to each scan (according to the manufacturer’s protocol) and fat mass index (FMI) will be calculated as total fat mass (kg) per height (meter) squared.

#### Early knee cartilage degeneration

Preliminary research links exercise therapy to better knee cartilage health in people at risk of post-traumatic OA (post-meniscectomy) [141] and early atraumatic OA up to 12-months [142, 143]. We will provide further insight over 24 months by quantifying changes in cartilage T2 relaxation times (sagittal multi-echo-spin-echo pulse sequences; 12 echoes) a widely used marker of early degeneration [60]. A senior imaging scientist will segment the cartilage manually and calculate average T2 for femoral, tibial, and patellar cartilage plates [144].

#### Therapeutic alliance

The 10-item Consultation and Relational Empathy (CARE) measure will be used to assess the quality of participants’ interactions with their physiotherapist [145, 146]. Each item is scored on a 5-point Likert scale, and items are summed to provide a total out of 50 points, with higher scores indicating greater empathy and interpersonal care. The CARE measure is valid, reliable, responsive, and sensitive [146].

#### Features of physiotherapy counseling that promote self-management

At the end of the 6-month intervention period, semi-structured 1:1 interviews will be conducted with a purposive maximum variation sample (gender, age, adherence, time since injury) [117] of 15–20 SOAR participants. Using video-cued narrative reflection [147], participants will self-select meaningful exchanges with their physiotherapist that promoted self-management while viewing a recording of their 1:1 initial action planning component of knee camp and a random weekly counseling session. Participants will be able to pause and rewind the recording to identify, describe, and elaborate on significant moments, verbal or non-verbal cues, or feelings. A definition of self-management [148] and context-specific examples will be provided. Probes and prompts will provide elaboration. Field notes will be taken, and interviews recorded. Ongoing analyses will inform sampling [117], and data collection will cease when no new themes are identified [118]. Video-recorded healthcare interactions are acceptable and provide valuable practice insights [149]. Video-cued interviews yield rich data as participants simultaneously identify, engage, and reflect on their lived experiences [147].

#### Intervention delivery costs

The cost to deliver the SOAR and minimal intervention control programs will be tracked by research personnel and reported.

#### Participant adherence

We will report intervention attendance, adherence behavior (Exercise Adherence Rating Scale [150] and Adherence to Exercise for Musculoskeletal Pain Tool [151]), and monthly step count (monthly SMS screen and Fitbit®) for both study groups, and percent partial and full exercise therapy and physical activity goal completion for the SOAR group.

#### Trial protocol

Enrollment procedure adherence, enrollment rate (percentage of those eligible who enroll), attrition rate (percentage of those who enroll but do not complete), assessment protocol compliance (percentage complete per follow-up), and adverse and unexpected events will be tracked. We will also assess physiotherapist fidelity (checklists refined in our pilot study applied to all recorded 1:1 sessions for 5 random participants/physiotherapist), intervention contamination (6-month survey question asking participants if they have interacted with anyone in the study receiving the other intervention), and participants’ expectation of benefitting from their assigned intervention (Credibility and Expectancy Questionnaire; CEQ, after the first 1:1 physiotherapist session) [152].

Adverse events will be defined as a health-related event requiring medical treatment, medications, and/or interfering with function for ≥2 days, which do not necessarily have a causal relationship with the treatment or any study intervention. Serious adverse events will include those that result in death, are life-threatening, require inpatient hospitalization or prolong existing hospitalization, result in persistent or significant disability/incapacity, or require intervention to prevent permanent impairment or damage. We will also collate unexpected events (an incident, experience or outcome that is unexpected, puts research participants at a greater risk of harm and may have been caused by the study procedures) [22].

### Stopping rules, intervention discontinuation {11b}

If the planned sample size is not reached within 36 months, we will halt recruitment at 132 participants, which will ensure 90% power to detect a clinically meaningful 10-point difference in KOOS_4_ 6-month response between treatment arms (anticipated 0.476 effect size). An intervention will be discontinued if any adverse event, medical condition, or situation occurs that makes continuing in the study not in a participant’s best interest.

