### Sample size {14}

The study sample size is based on a primary analysis of superiority of the 6-month KOOS_4_ response to the SOAR program considering pilot RCT data [54], systematic review of meaningful KOOS_4_ thresholds in the study population [42] and typical ACLR and knee OA exercise programs effect sizes (0.45–0.50) [40, 74]. Using a KOOS_4_ response standard deviation of 21 points (pilot RCT), α = 0.05 and 1 − ß = 90%, 66 people/group (regression model with 4 covariates and combined *r*^2^ = 0.3) are needed to detect a mean between group KOOS_4_ minimal important difference (10 points) [42], which is consistent with a 0.476 effect size. A sample of 166 (83/group) allows for 20% attrition. Calculations were done with the analysis of covariance procedure in Power Analysis and Sample Size 13 (NCSS, USA) [75].

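### The fallback rule claims 90% power for 132 recruited participants, but 132 is the number needed with outcome data; after the plan's own 20% attrition, power is about 83%

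*Protocol article*

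**What the plan says.** Two sections of the protocol article use the number 132.

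- **Sample size {14}.** For the 6-month KOOS4 response, the inputs are an SD of 21 points from the pilot trial, α = 0.05, 90% power, a 10-point difference and a "regression model with 4 covariates and combined" r² of 0.3. The requirement is "66 people/group", which is 132 in total, for a difference described as one "which is consistent with a 0.476 effect size". The section then states: "A sample of 166 (83/group) allows for 20% attrition".
- **Stopping rules, intervention discontinuation {11b}.** If the planned sample is not reached within 36 months, "we will halt recruitment at 132 participants, which will ensure 90% power to detect a clinically meaningful 10-point difference". The same standardised effect of 0.476 is cited. This section makes no allowance for attrition, and no other section adds one for the fallback.

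**The concern.** In the Sample size section, 132 is what must remain after losses; that is why 166 are to be recruited. In the stopping rule, 132 is the count at which recruitment ends, yet the same power is claimed for the same difference. The two statements agree only if there is no loss at 6 months. If 132 recruits really gave 90% power under the plan's assumptions, the increase to 166 would serve no purpose.

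The power figure is the only justification given for the fallback. The Discussion names recruitment and differential loss to follow-up as potential challenges, so slow accrual and attrition could well occur together. The team would then stop early in the belief that power was intact, and a null result would be read against 90% power that the trial did not have.

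**Working it through.** **Inputs (Sample size {14} unless noted)**

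- SD of the KOOS4 response: 21 points
- Four covariates, combined r² = 0.3
- Difference to detect: 10 points (10/21 = 0.476)
- α = 0.05. Sidedness is not stated; two-sided is assumed (see step 1).
- Attrition: 20%
- Allocation 1:1 (Study design {8})
- Fallback recruitment: 132 (Stopping rules {11b})

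**Method.** ANCOVA power from the noncentral t distribution, with n analysed per group:

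- residual SD = 21 × √(1 − 0.3) = 17.57
- adjusted effect = 10 / 17.57 = 0.569
- noncentrality = 0.569 × √(n/2)
- degrees of freedom = 2n − 2 − 4 = 2n − 6

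**Step 1: reproduce the plan's figure.**

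- n = 65: power 89.6%
- n = 66: noncentrality = 0.569 × √33 = 3.27, power 90.05%

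So 66 per group is the smallest size that reaches 90%, as the plan states. Other readings do not reproduce it: by the normal approximation, a one-sided test needs 53 per group, and a two-sided test without covariate adjustment needs 93 per group.

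**Step 2: reproduce the attrition allowance.** 66 / 0.8 = 82.5, rounded up to 83 per group, or 166. In reverse, 166 × 0.8 = 132.8 analysed, which gives 90.2% power. This confirms that 132 is the number needed with outcome data.

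**Step 3: apply the same allowance to the fallback.** 132 × 0.8 = 105.6 analysed, or 52.8 per group. Noncentrality = 0.569 × √26.4 = 2.92, and power is 82.5%. In whole participants, 105 analysed gives 82.3% and 106 gives 82.7%. The normal approximation gives 83.3%.

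**Step 4: vary the loss at 6 months.**

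| Loss among 132 recruited | Analysed | Power |
|---|---|---|
| 0% | 132.0 | 90.05% |
| 5% | 125.4 | 88.5% |
| 10% | 118.8 | 86.8% |
| 15% | 112.2 | 84.8% |
| 20% | 105.6 | 82.5% |
| 25% | 99.0 | 80.0% |

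There is no slack at the top of the table: 131 analysed already gives 89.8%.

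**Step 5: detectable difference.** With 52.8 per group, the difference detectable with 90% power is 11.19 points by the noncentral t and 11.08 by the normal approximation, against the stated 10. For a true 10-point difference, the type II error is 100% − 82.5% = 17.5% rather than 10%.

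**The case against.** The strongest case on the other side has four parts.

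- **The 20% may not apply at 6 months.** The Sample size section gives no time point, and the Trial protocol section defines attrition as enrolling without completing, in a study that runs to 24 months. Loss at 6 months could be smaller. This is a fair reason to state the shortfall conditionally. However, the plan applies the 20% to a calculation for the 6-month response, so that is the natural reading, and even 5% loss leaves 88.5%.
- **The model uses all available data.** The Analyses section {20a, b, c} plans likelihood-based estimation partly to limit loss of power. Later visits may recover a little information about a missing 6-month value, but they cannot recover all of it. The plan's own sample size takes no credit for any recovery and counts attrition in full.
- **132 might mean completers.** The wording does not support this. The rule concerns halting recruitment, and the planned sample it refers to is the 166 to be enrolled.
- **The consequences are limited.** This objection stands. The rule is a contingency, and the main design delivers its 90%. Type I error, the estimand and the primary analysis are unaffected. Power of 80% to 89% over a loss of 25% down to 5% is respectable, and a reported confidence interval would show the precision achieved. It bears on how much the error matters, not on whether the stated figure is right.

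**Conclusion.** The concern holds. The stopping rule reuses the number required after attrition as the number recruited, and its claim to ensure 90% power fails with the loss of even one participant. Under the plan's own 20% attrition, taken to apply at 6 months, power is about 83% (82.5% by the noncentral t, 83.3% by the normal approximation), and the difference detectable with 90% power is about 11.2 points. At 10% loss, power is 86.8%. These figures rest on the plan's SD, r² and covariate count, on a two-sided 5% test, and on counting each missing 6-month outcome as a full loss, as the plan's own allowance does. The fallback remains usable; its stated power is wrong.

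**What to change.** Replace the power statement in Stopping rules {11b} with one consistent with Sample size {14}, for example: halting at 132 randomised participants gives about 83% power to detect a 10-point difference if 20% are lost by 6 months, and 90% only if all have 6-month KOOS4 data. It would help to say in Sample size {14} that the test is two-sided and at which visit the 20% applies.

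The cost is a sentence in the protocol, with a matching registry update if the rule is recorded there. It needs no extra participants and no design change; the only effect is a less favourable stated power for the fallback. Recruitment began on May 22, 2024, so if the 36 months run from that date, the correction should be made before about May 2027.

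Redefining the threshold as 132 participants with an observed 6-month KOOS4 would also remove the contradiction, but it defeats the purpose of the rule. At 20% loss it requires 132 / 0.8 = 165 recruits, essentially the target that the rule assumes was missed. Restating the power is the better change.
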